## Abstract

**Background:**

Human papillomavirus (HPV) infection is the primary cause of cervical cancer, and HPV self-sampling has emerged as a novel screening method with the potential to increase screening coverage and early detection of cervical cancer. However, the implementation of HPV self-sampling in China faces several challenges, including sociocultural factors, economic burdens, and low feedback rates. This study will aim to improve the feedback rate of HPV self-sampling results through a Pay-It-Forward approach and explore its impact on HPV positivity rates and subsequent treatment compliance.

**Methods:**

This study employs a randomized controlled trial (RCT) design, enrolling women aged 24 and older who have not received the HPV vaccine and have not undergone HPV self-sampling or cervical cancer screening in the past 12 months. Participants will be randomly divided into a control group (free distribution of HPV self-sampling kits) and an intervention group (pay up front for HPV self-sampling). The prepayment amount is 20 RMB, which is fully refunded upon completion of the self-sampling and feedback of results. The primary outcome measure is the feedback rate of HPV self-sampling results. The study is conducted at maternal and child health care and family planning service centers in Hohhot, Inner Mongolia Autonomous Region, with an expected enrollment of 108 participants.

**Discussion:**

The Pay-It-Forward approach is expected to significantly improve the feedback rate of HPV self-sampling results by enhancing participants’ psychological commitment and sense of responsibility. Additionally, this strategy may positively affect HPV positivity rates and subsequent treatment compliance. The innovation of this study lies in the first application of the Pay-It-Forward method to HPV self-sampling and the comprehensive analysis of urban-rural differences. The results of this study will provide a scientific basis for improving women’s cervical health awareness and optimizing HPV self-sampling intervention strategies, thereby promoting the widespread application of HPV self-sampling in cervical cancer screening.

**Trial registration:**

This study registered at ClinicalTrials.gov (ChiCTR2500095770) on January 13, 2025.

## Global status of HPV infection

1

Human papillomavirus (HPV) is a common sexually transmitted virus. In 2007, an estimated 291 million women worldwide were infected with HPV (1, 2). The infection is particularly prevalent among sexually active women, especially those under 25, with the highest infection rate, which decreases with age (3). Studies show a positive correlation between HPV infection rates and the severity of cervical lesions (4). Additionally, HPV-related diseases impose substantial economic burdens on healthcare systems, with direct costs ranging from 47.16 million to 1.8 billion yuan (5).

In China, HPV epidemiology mirrors global trends but has unique aspects. Studies indicate an overall HPV infection rate of 13.1% - 18.8% in the general population, with high-risk HPV at 12.95% - 17.1% and low-risk HPV at about 3.28% (6). HPV is a major cause of cervical cancer (7).

## The importance of HPV screening in cervical cancer prevention

2

Cervical cancer is preventable and controllable. In 2020, the World Health Assembly adopted the Global Strategy to Accelerate the Elimination of Cervical Cancer, setting the 90-70–90 goals for 2030: 90% of girls vaccinated against HPV by 15, 70% of women screened at least once by 35-45, and 90% of diagnosed women treated (8, 9). In China, these measures could prevent 7.509 million new cases and 2.529 million deaths between 2021 and 2100 (10).

Despite HPV vaccines’ effectiveness, regular screening remains vital. HPV screening detects infections and cervical intraepithelial neoplasia (CIN) early, enabling timely intervention (11). Regular screening significantly improves early cervical cancer detection and reduces advanced cancer incidence (12). Early identification of high-risk HPV infections allows for timely management, as these individuals are more likely to develop precancerous lesions or invasive cancer (13). Thus, regular HPV screening is key to reducing cervical cancer incidence and mortality (14).

## Introduction and challenges of HPV-based self-sampling

3

HPV-Based Self-Sampling is an emerging method allowing women to collect samples at home for HPV testing, aiming to improve screening coverage in areas with limited resources or low compliance. It typically involves using specially designed tools to collect vaginal or cervical swabs, sent to labs for testing (15).

HPV-Based Self-Sampling offers several advantages. It provides privacy, allowing women to comfortably, reducing awkwardness and discomfort (16). Self-sampling is often painless and less expensive than traditional methods, increasing women’s willingness to participate (17). Studies show self-testing results are highly consistent with traditional clinical sampling, indicating it can effectively replace conventional screening, especially in enhancing coverage and early HPV detection (18).

However, challenges remain. The accuracy of self-sampling technology needs attention, as issues like insufficient sample collection or improper operation may affect results (19). Participant acceptance is also key; some women may be unfamiliar with or lack confidence in self-sampling methods, affecting participation rates (20). Ensuring timely sample submission and efficient lab processing during self-examination is crucial for result validity (21).

## Current situation and challenges of HPV-based self-sampling in China

4

In China, HPV-Based Self-Sampling aims to improve screening coverage and early cervical cancer detection but faces multiple challenges. The Chinese government and health departments recognize the importance of HPV screening in cervical cancer prevention and have promoted this method. HPV testing is included in cervical cancer screening programs, with free or subsidized screening launched in some areas (22). These measures have improved women’s screening coverage, but the overall self-examination rate is still low, partly due to insufficient publicity, inconvenient transportation, and economic burdens (23). Despite subsidies, HPV-Based Self-Sampling’s nationwide coverage is far below that of many developed countries (24).

In Inner Mongolia, a region characterized by complex geography and a dispersed population, HPV-based self-sampling has shown significant potential in enhancing screening coverage. Studies have demonstrated that self-sampling is highly acceptable and effective in resource-limited settings, particularly in rural and remote areas where traditional screening methods face implementation challenges (25). This approach offers privacy, convenience, and cost-effectiveness, making it a promising strategy to overcome geographical and resource barriers in cervical cancer screening (25).

## Factors affecting the feedback rate of HPV-based self-sampling results

5

Unique socio-cultural factors in China significantly influence the acceptance and feedback rate of HPV-Based Self-Sampling. Traditional beliefs and attitudes towards sexual health can create cognitive barriers and lead to low acceptance among women (26). Some women lack confidence in self-examination or awareness of HPV risks, affecting their compliance (27). Insufficient resource allocation in rural areas is also a major challenge, reducing rural women’s opportunities for HPV screening and subsequent treatment (28). Differences in HPV testing quality between regions and institutions, and a lack of unified quality control standards, may affect test accuracy and reliability (29). Socio-economic factors, such as income level and occupation type, significantly impact women’s willingness and ability to access and provide feedback on HPV screening services (30). Cultural and educational factors also play a role, in conservative cultures, women may feel ashamed about self-examination involving private parts, and less educated women may lack relevant health knowledge, leading to lower participation (26, 31). Healthcare system factors, including uneven medical resource distribution and varying screening service quality, further constrain women’s access to HPV screening services (32, 33).

## Current intervention measures and limitations for improving the self-sampling feedback rate of female HPV

6

The refundable deposit mechanism, grounded in behavioral science and behavioral economics, leverages the sunk cost effect and present bias to enhance participant engagement (34). By requiring participants to pre-pay a fee that is refunded upon completing self-sampling and feedback, this strategy increases psychological commitment and motivation to complete the process. This approach not only reduces economic barriers but also promotes timely sample submission and feedback, thereby improving screening outcomes and participant compliance. Studies have shown that such mechanisms can significantly enhance adherence to health screening programs by creating a sense of responsibility and investment among participants (35).

Health education and publicity interventions, based on the Health Belief Model and Social Cognitive Theory, aim to improve the self-sampling feedback rate of female HPV. These interventions have been shown to increase self-sampling rates, particularly among low-income women through community health education programs and among young women via social media (36). However, their effectiveness is limited by information dissemination channels and audience health awareness levels (37), and their impact is often short-term, lacking mechanisms for long-term tracking and sustained intervention (38). Economic incentive measures, such as providing free self-sampling reagents or cash rewards, have significant short-term effects based on behavioral economics theory (39). These measures increase the feedback rate of self-sampling by reducing participants’ economic burden (38), but their long-term effects and fairness still need further exploration (40). Interventions to improve self-sampling reagents and techniques, based on the Technology Acceptance Model and User Experience Theory, aim to enhance user experience. However, their promotion and popularization still require time and resources, potentially leading to uneven coverage among different populations (37). Community support and mobilization, based on Social Capital Theory and Community Mobilization Theory, have played an important role in improving the feedback rate of HPV self-sampling. However, the effectiveness of this intervention depends on the adequacy of community resources and the ability to mobilize personnel, and in communities with limited resources, the implementation effect may be constrained (41).

However, the prepaid strategy, based on the Sunk Cost Effect and Present Bias, emphasizes the impact of economic input on behavioral persistence (42). Prepaid interventions have been shown to significantly improve the feedback rate of HPV self-sampling (37). This strategy enhances participants’ psychological commitment to self-sampling behavior and increases their motivation to complete it (43). It further incentivizes participants to complete self-sampling by promoting the recovery of paid fees, improving the feedback rate and increasing attention to the detection process (44).

This study will focus on women in the high-risk age group for cervical cancer, especially those who have never undergone HPV-Based Self-Sampling or cervical cancer screening. We will use a randomized controlled trial (RCT) design to improve the feedback rate of HPV self-sampling results through prepaid intervention and explore the feasibility and effectiveness of HPV-Based Self-Sampling in cervical cancer screening. The impact of prepaid intervention on HPV positivity rates and subsequent diagnosis and treatment compliance will also be investigated. Further research is needed on factors influencing the improvement of feedback rates through new prepaid interventions, such as participants’ age, education level, and income level. Additionally, evaluating participants’ satisfaction with the entire HPV self-test intervention process can provide insights into the acceptance of the measures during implementation, further enhancing women’s awareness of cervical health and promoting the application of HPV-Based Self-Sampling in female cervical cancer screening, providing a scientific basis.

## Methods

7

### Objective

7.1

The primary objective of this study is to evaluate the effectiveness of a Pay-It-Forward approach compared to free distribution of HPV self-sampling kits in improving the feedback rate of HPV self-testing among women in China. We hypothesize that the Pay-It-Forward intervention group will achieve a significantly higher HPV self-testing feedback rate than the free distribution control group. Additionally, we aim to assess whether the Pay-It-Forward intervention leads to higher HPV positivity rates and better adherence to subsequent diagnostic and treatment procedures compared to the control group.

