##### HPV positivity rate and subsequent treatment adherence

7.11.2.1

The HPV positivity rate, defined as the proportion of participants testing positive for HPV through self-sampling, will be calculated based on laboratory-confirmed results using standardized PCR techniques. Data will be collected from certified laboratories, with a subset of samples retested for validation. Subsequent treatment adherence will be assessed by tracking participants’ attendance at recommended follow-up appointments and receipt of appropriate treatments following a positive HPV result. This will be monitored through electronic medical records and phone follow-ups at 1 and 3 months post-notification. Adherence will be recorded as a binary outcome and expressed as a percentage of participants who follow through with recommended care.

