### Follow-up

7.12

This is a six-month study and the intervention will be implemented during the first four weeks of subject enrollment. All subjects participating (both the “Pay-It-Forward” group and control group) are required to finish electronic questionnaires at two time points, including baseline and post intervention. The content of the follow-up visits varied across time points, with sociodemographic information and baseline health data collected only at baseline. Behavioral information, HPV self-sampling results, and participant satisfaction data will be collected at the 4-week post-intervention follow-up point. The specific follow-up and related data collection schedule is shown in **Table 1**.

**Table 1 T1:** Variables and measures collected at every time points.

Variables		Date source	Study Period	Baseline (T0)	Post-intervention (T1)
			timepoint	0w ± 1w	4w ± 1w
Intervention preparation	\	\	Informed consent	✓	\
	\	\	Random grouping	✓	\
	\	\	Online consulting service	✓	✓
Covariates	Individual	Baseline questionnaire	Sociodemographic information	✓	\
	Individual	Baseline questionnaire and Follow-up questionnaire	Behavioral information	✓	✓
Primary outcome	Feedback rate of HPV self-sampling	Laboratory records	Percentage of participants who return the HPV self-sampling kit within 1 month	\	✓
HPV infection status (Secondary Outcome)	HPV positivity rate	Laboratory records	Proportion of participants with lab-confirmed HPV-positive results (PCR testing)	\	✓
HPV self-sampling cognition and acceptance (Secondary Outcome)	HPV Self-Sampling Awareness	Follow-up questionnaire	HPV Self-Sampling Awareness Questionnaire	\	✓
	HPV self-sampling Satisfaction	Follow-up questionnaire	HPV self-sampling Satisfaction Questionnaire	\	✓
	HPV Self-Sampling Acceptance	Follow-up questionnaire	HPV Self-Sampling Acceptance Scale	\	✓
Cervical cancer health literacy and attitudes (Secondary Outcome)	Cervical Cancer-related Knowledge	Baseline questionnaire	Cervical Cancer-related Knowledge Scale	✓	\
	Cervical Cancer Screening and HPV Vaccination Attitude	Baseline questionnaire	Cervical Cancer Screening and HPV Vaccination Attitude Scale	✓	\
Psychology status (Secondary Outcomes)	depressed	Baseline questionnaire	PHQ-9	✓	\
	Anxiety	Baseline questionnaire	GAD-3	✓	\
	Stress	Baseline questionnaire	PSS-4	✓	\
	Family health	Baseline questionnaire	FHS-SF	✓	\
	Social support	Baseline questionnaire	PSSS-SF	✓	\
	personalities	Baseline questionnaire	BFI	✓	\

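### The HPV positivity denominator is not fixed and adherence is assessed only among tested positives, so the aim of attributing either to the deposit has no clear randomised comparison behind it

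*Protocol article*

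**What the plan says.** Section 7.1 ties its formal hypothesis to the feedback rate alone and then adds a further aim: "Additionally, we aim to assess whether the Pay-It-Forward intervention leads to higher HPV positivity rates", along with better adherence to later diagnosis and treatment.

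Section 7.11.2.1 gives the outcome as "The HPV positivity rate, defined as the proportion of participants testing positive for HPV through self-sampling". Table 1 in section 7.12 has "Proportion of participants with lab-confirmed HPV-positive results (PCR testing". Neither says which participants form the denominator. The primary outcome in 7.11.1, by contrast, is explicitly divided by all kits distributed, and a kit not received within one month counts as no feedback.

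Adherence in 7.11.2.1 covers attendance at follow-up and "receipt of appropriate treatments following a positive HPV result", "expressed as a percentage of participants who follow through with recommended care".

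Section 7.13 applies multiple imputation to missing data, treating the missingness as random, and exempts no outcome. Section 7.7, written for the deposit arm, describes care without charge after a positive result. Section 7.10, for controls, describes information and referral.

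**The concern.** Randomisation makes the expected HPV prevalence equal in the two arms, and a 20 RMB refundable deposit cannot alter it. The deposit can alter how many kits come back and from whom. What a higher positivity rate means therefore depends on a denominator that the article leaves open. Under one reading it measures how many infections the strategy finds. Under another it measures the make-up of the women who returned a kit.

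Adherence has a firmer problem. A woman enters that outcome only after returning a kit and testing positive, both of which happen after randomisation, and the first is what the intervention is meant to change.

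At stake is a published statement that the deposit raised or lowered positivity or adherence when the comparison behind it may not be a randomised one. The primary outcome is not affected.

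**Working it through.** **Inputs.** Return rates r1 = 0.90 (deposit) and r0 = 0.617 (control), and 54 women per arm, from section 7.5. Prevalence 13.1% to 18.8%, the general-population range in section 1. Assumed here, not in the documents: women who return without a deposit would also return with one; the extra returners have k times the positivity of control returners, with k from 0.5 to 2; true adherence is 50% to 80%.

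**The plan's own figure.** No sample size or power is given for positivity or adherence. For the primary outcome, 90% versus 61.7%, two-sided 5%, 80% power with continuity correction gives 42 per arm. With 20% dropout, 42/0.8 = 52.5, so 53, within one of the stated 54. The 54 per arm is used below.

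**Returners and positives.**
- Returners: 54 × 0.90 = 48.6 versus 54 × 0.617 = 33.3.
- Positives at 13.1%: 6.4 versus 4.4. At 18.8%: 9.1 versus 6.3.

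**Reading A: positivity among returned kits.** With π the positivity of control returners, the deposit arm's positivity is [r0·π + (r1 − r0)·k·π]/r1. The difference is therefore π(k − 1)(r1 − r0)/r1, where (r1 − r0)/r1 = 0.283/0.90 = 0.314.

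| π | k = 0.5 | k = 1 | k = 2 |
|---|---|---|---|
| 13.1% | −2.1 points | 0 | +4.1 points |
| 18.8% | −3.0 points | 0 | +5.9 points |

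The sign depends entirely on k, that is, on who the extra returners are.

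**Reading B: all randomised, unreturned results imputed under the general rule of 7.13.** The target becomes prevalence in each arm. Randomisation makes the expected difference zero, so there is no effect of the deposit to find.

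**Reading C: all randomised, unreturned kit counted as not detected.** The difference is (r1 − r0)·k·π.

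| π | k = 0.5 | k = 1 | k = 2 |
|---|---|---|---|
| 13.1% | +1.9 points | +3.7 points | +7.4 points |
| 18.8% | +2.7 points | +5.3 points | +10.6 points |

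At k = 1 the rates are 11.8% versus 8.1% (13.1% prevalence) and 16.9% versus 11.6% (18.8%). Power with 54 per arm, two-sided 5%, normal approximation, is about 9% and 12%. It reaches 31% at the most favourable corner (18.8%, k = 2).

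**Adherence among positives.** The 95% half-width is 1.96·√[p(1 − p)(1/m1 + 1/m0)], where m1 and m0 are the expected positives.
- Narrowest (18.8%, p = 0.8): 1.96 × √[0.16 × (1/9.14 + 1/6.26)] = 0.41.
- Widest (13.1%, p = 0.5): 1.96 × √[0.25 × (1/6.37 + 1/4.36)] = 0.61.

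The normal approximation is crude at these counts, but the order of size is clear. As a check, the power of Fisher's exact test for an assumed 90% versus 50% adherence is about 19% with 6 versus 4 women and 32% with 9 versus 6.

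**The case against.** The strongest reply is that the article never restricts positivity to returned kits. Taken literally, a proportion of participants is a proportion of everyone enrolled, which is Reading C: a valid randomised comparison in which a higher rate is the expected direction, because more kits come back. That stands. A reader might infer that any positivity difference can only be selection, or that the article hypothesises an effect on infection. The text supports neither. The denominator is open, and 7.1 words this as an aim to assess. The openness remains a defect, because 7.11.1 fixes its own denominator and states how non-return is counted, while the positivity definition does neither.

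A reader might also infer that 7.13 commits the trial to imputing HPV results for unreturned kits. It does not say so, and it plans sensitivity analyses on missing-data assumptions. What stands is that the printed rule is general and does not exclude this.

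A lower positivity in the deposit arm despite more infections found is a possible outcome, not a predicted one. It requires the extra returners to be at lower risk, and nothing in the documents establishes that.

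For adherence, selection is not the only possible explanation of a difference, since the deposit might itself affect follow-through. That does not restore the protection of randomisation.

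Finally, it is tempting to see a contradiction between "This will be monitored through electronic medical records and phone follow-ups at 1 and 3 months post-notification" and participants being "required to finish electronic questionnaires at two time points, including baseline and post intervention". There is none: the latter concerns questionnaires only, and section 7.12 describes a six-month study. The absence of an adherence row from Table 1 is editorial.

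**Conclusion.** The point holds in limited form. The aim in 7.1 attributes positivity and adherence to the deposit, but only one of three available readings of positivity supports such a claim, and the article does not select it. Among returned kits the contrast can take either sign, about −2 to +4 points at 13.1% prevalence and −3 to +6 at 18.8%. These ranges rest on k between 0.5 and 2 and on the return rates assumed in 7.5. With imputation of unreturned results, the quantity compared is one a deposit cannot change. Adherence as defined is not a randomised comparison and would be estimated to within about ±41 to ±61 points for assumed adherence of 50% to 80%. The differing descriptions of care after a positive result in 7.7 and 7.10 would confound it further. This is a matter for secondary outcomes that should be corrected before analysis.

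**What to change.** In 7.1 and 7.11.2.1, define two comparative outcomes over all randomised women: (a) HPV-positive detected; (b) HPV-positive detected and recommended follow-up completed. A woman with no returned kit counts as not detected, so she scores no on both. In 7.13, state that HPV results for unreturned kits are not imputed. Report positivity among returned kits and adherence among positives as descriptive counts, with no causal claim between arms. Reconcile 7.7 and 7.10 on care after a positive result before any adherence comparison is made. While Table 1 is open, add an adherence row with its 1- and 3-month contacts.

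The cost is rewording, with no new data or visits. The downside is that both outcomes serve estimation only: power for (a) is about 9% to 12% if positivity is the same in all women. The text should say so and give confidence intervals.
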